## **6.2. Statistical Significance and Multiple Comparisons:**

Statistical significance will be defined as a two-tailed p-value  $< 0.05$ . For general statistical analyses, Bonferroni correction or other correction methods will be applied to address multiple comparisons where appropriate. For neuroimaging analyses, more specialized methods for multiple comparison correction will be considered, including Family-Wise Error (FWE) rate, False Discovery Rate (FDR), permutation testing, or Monte Carlo simulation, with significance also defined at a p-value  $< 0.05$ . The specific correction method will be chosen based on the nature of the analysis and data characteristics

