### **6.1. General Principles and Methods**

- (1) Cross-sectional between-group comparisons: For continuous demographic variables, one-way ANOVA or t-test will be employed. Categorical variables will be compared using Fisher's exact test. For other cross-sectional comparisons of neuroimaging, clinical,

neurophysiological, and neuropsychological characteristics between groups, independent t-tests, chi-squared tests, or analysis of covariance (ANCOVA), or multiple linear regression analysis will be utilized, as appropriate. Potential covariates such as age, sex, and other relevant factors, will be considered, as necessary.

- (2) Longitudinal Analyses: To assess longitudinal changes in neuroimaging, clinical, neurophysiological, and neuropsychological measures, repeated measures ANCOVA or linear mixed-effects models will be employed. These models are robust for handling within-subject correlations and missing data inherent in longitudinal designs.
- (3) Assessment of Associations: Correlations between clinical severity, scale scores, and other assessment findings will be examined using Pearson's correlation or Spearman's correlation. To control for potential confounding variables and assess independent relationships, multiple linear regression or linear mixed-effects models will be used, as appropriate.
- (4) Neuroimaging-Specific Analyses:
  - Structural and Functional Brain Changes: We will compare and analyze structural and functional brain changes between groups.
  - MRS Neurometabolite Analysis: For the analysis of individual MRS neurometabolites, the LCModel or appropriate post-processing tools will be used.
  - Graphical Analysis and Presentation: For graphical analysis and presentation of brain imaging data, SPM (Statistical Parametric Mapping) and FSL (FMRIB Software Library), or other neuroimaging analysis softwares will be utilized.

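### For the non-imaging tests, section 6.2 names only Bonferroni; Holm's step-down would give the same familywise protection, never reject less, and gain a little to moderate power

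*Protocol*

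**What the plan says.** Protocol section 6.2 sets the threshold first: "Statistical significance will be defined as a two-tailed p-value" below 0.05. It then treats two groups of analyses separately.

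- **General analyses:** "Bonferroni correction or other correction methods will be applied to address multiple comparisons where appropriate". No method other than Bonferroni is named.
- **Imaging:** "For neuroimaging analyses, more specialized methods for multiple comparison correction will be considered, including Family-Wise Error (FWE) rate, False Discovery Rate (FDR), permutation testing". A Monte Carlo approach is listed as well. Bonferroni is not named here.

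The section closes by leaving the choice open: "The specific correction method will be chosen based on the nature of the analysis and data characteristics".

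Section 6.1(1) shows what falls under the general sentence. Besides imaging, it compares clinical measures and "neurophysiological, and neuropsychological characteristics between groups, independent t-tests, chi-squared tests, or analysis of covariance (ANCOVA), or multiple linear regression analysis will be utilized, as appropriate". Section 5(3) lists eight questionnaire constructs (depression, anxiety, alcohol use, smoking, suicide, resilience, anger, impulsivity), and section 5(6) adds a neuropsychological battery over several cognitive domains. MRS metabolites are handled elsewhere, as a bullet under the neuroimaging-specific analyses in section 6.1(4): "For the analysis of individual MRS neurometabolites, the LCModel or appropriate post-processing tools will be used".

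**The concern.** Bonferroni compares every p-value in a family of m tests with 0.05/m. Holm orders the p-values and compares the smallest with 0.05/m, the next with 0.05/(m−1), and so on up to 0.05, stopping at the first failure. Both hold the familywise error at 0.05 whatever the dependence between tests. For accept/reject decisions Bonferroni is therefore dominated.

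What is at stake is how many real differences are identified within a battery, not whether any is found and not whether false positives are controlled. That matters somewhat here, because section 2 aims to identify the several factors behind differing outcomes. An analyst who follows the one method named would use the less powerful of two equally protective procedures.

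**Working it through.** **Inputs from the protocol.** Two-sided 0.05 (section 6.2). The protocol states no number of tests per family, sample size, effect size, correlation or power, so it has no figure to reproduce. Everything quantitative below is assumed.

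**Step 1: Holm rejects everything Bonferroni rejects.** If Bonferroni rejects a hypothesis, its p-value and every smaller one are at most 0.05/m. All of Holm's thresholds are at least 0.05/m, so Holm reaches that hypothesis and rejects it too.

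**Step 2: same familywise error.** Let m₀ hypotheses be true nulls. The first true null that Holm wrongly rejects comes no later than step m − m₀ + 1, where the threshold is 0.05/m₀. A familywise error therefore needs some true null with p ≤ 0.05/m₀. By the union bound its probability is at most m₀ × 0.05/m₀ = 0.05, under any dependence.

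**Step 3: thresholds for m = 8** (the number of constructs in section 5(3), used as an illustration).
- Bonferroni: 0.05/8 = 0.00625 for every test.
- Holm: 0.05/8 = 0.00625, 0.05/7 = 0.0071, 0.05/6 = 0.0083, 0.05/5 = 0.0100, 0.05/4 = 0.0125, 0.05/3 = 0.0167, 0.05/2 = 0.025, 0.05.

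The first thresholds are equal, so the two methods reject at least one hypothesis in exactly the same data sets. Any gain lies in the second and later rejections.

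**Step 4: size of the gain.** Simulation with 100,000 sets of equicorrelated normal statistics per setting, correlation 0.3. Real effects are shifted by z(1 − 0.05/(2m)) + z(target power under Bonferroni). For m = 8 and 60% this is 2.734 + 0.253 = 2.988 before rounding of the parts. Mean power per real effect:

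| Tests m | Real effects | Bonferroni | Holm | Gain (points) |
|---|---|---|---|---|
| 8 | 2 | 0.699 | 0.709 | 1.0 |
| 8 | 4 | 0.699 | 0.734 | 3.5 |
| 10 | 5 | 0.599 | 0.635 | 3.6 |
| 6 | 6 | 0.602 | 0.714 | 11.2 |
| 8 | 8 | 0.600 | 0.719 | 11.9 |
| 10 | 10 | 0.601 | 0.726 | 12.5 |

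In the three settings with some true nulls, Holm's familywise error was 0.037 to 0.042. A repeat of the six settings with a different random seed agreed to within 0.003 in every power figure and found no hypothesis rejected by Bonferroni alone.

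**Step 5: other assumptions.** A second grid took m = 5, 10 or 20, correlation 0 or 0.5, and single-test power of 80% or 95% before adjustment, with 60,000 replicates. Gains were 0.0 to 0.1 points with one real effect, about 1.3 to 4.2 with about half real, and about 7 to 16 with all real. Power to detect at least one real effect moved by at most about 0.1 point. Holm's largest familywise error was 0.049.

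**The case against.** The strongest objection is that the protocol makes no commitment to criticise. A reader might infer that Bonferroni is the fixed default and that power is therefore lost. The text does not support that: the same sentence admits other methods, Holm among them, and the last sentence of section 6.2 leaves the choice open. Loss follows only where Bonferroni is actually used. This stands.

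A reader might also extend the point to the metabolite tests. Section 6.1(4) groups MRS with neuroimaging, and the neuroimaging sentence of section 6.2 does not name Bonferroni, so those tests are left out here.

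The gain of 11–13 points should not be the headline. It needs every outcome in a family to be truly affected. That several measures differ together is plausible, since section 4.2 excludes psychiatric disorder only from the unexposed group, but the protocol does not state it.

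Finally, Bonferroni is valid, gives simple simultaneous confidence intervals, and could be replaced in a separate SAP that is not shown. All true, and the reason this is a minor point. It does not remove it: the protocol has chosen to name one method, and a better one for significance decisions can be named at no cost in data. Naming it in advance also avoids a later move away from Bonferroni that could look driven by results.

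**Conclusion.** The point holds as an optional improvement of low severity. Where Bonferroni is applied to the clinical, questionnaire and cognitive families, Holm is never worse for significance decisions and has the same familywise guarantee; that part is exact and needs no assumptions.

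The size is assumption-bound. With 6–10 tests, correlation 0.3 and 60–70% per-test power under Bonferroni, average power rises by about 1 point with few real effects, 3–4 points with about half real, and 11–13 points only with all real. The chance of at least one rejection is essentially unchanged. The documents do not support saying that the protocol contains an error, that it binds the analysts to Bonferroni, or that a particular amount of power will be lost.

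**What to change.** Two changes in section 6.2 are needed together:

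1. For the general analyses, replace the reference to Bonferroni or other methods by *Holm's step-down correction within each family of outcomes*.
2. Limit the closing sentence on choosing the method by data characteristics to the neuroimaging analyses.

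Swapping the name alone would secure nothing, because the open alternative would bind analysts to Holm no more than the present text binds them to Bonferroni. Imaging and MRS metabolite analyses stay under the neuroimaging sentence.

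The cost is a short wording change, with no extra participants or data. The families must be listed before analysis, which is a further task and can be done in the SAP; Bonferroni needs them as well. Simultaneous confidence intervals become less simple than with Bonferroni.
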